## 5. Significance and Background of the Problem

The early childhood period, from birth to age six, is crucial for a child's cognitive and emotional development, as it is a time when the brain rapidly develops. Once this period has passed, it is challenging to correct developmental errors. This development heavily depends on social and environmental stimuli, making the family environment particularly significant, as children spend most of their time with their families during this stage. Studies have shown that quality family time can significantly enhance children's academic performance and reduce future behavioral problems. Additionally, developmental support during this phase is linked to a 25% increase in income when children reach adulthood.

However, currently, early childhood does not receive sufficient stimulation from families, leading to missed opportunities for full potential development. A survey found that 43% of children in low- to middle-income countries face this issue, which is due to a combination of factors, including a lack of knowledge and appropriate attitudes toward early childhood upbringing, increased maternal employment outside the home compared to the past, and beliefs that education is the responsibility of schools rather than parents. Some parents even feel they lack the capability to support their child's development. Furthermore, many parents allow their children to spend most of their time on mobile phones,

leading to a higher rate of early childhood mobile addiction. Therefore, promoting effective family time during early childhood is crucial.

One key factor influencing parents' roles in promoting child development is parental empowerment, which refers to the process and psychological outcome where parents feel capable of managing and handling their parenting roles effectively. Previous research indicates that parents who feel empowered perform better in their roles and actively engage in supporting their child's development and education at school. Thus, increasing parental empowerment is a sustainable way to foster children's development.

Our research team has recognized this issue and aims to create activities that enhance parental empowerment to promote children's cognitive and educational development. The focus will be on working parents who have limited time to support their child's development. The activities are based on the principle of "Parents as Agents of Change," meaning that parents will act as mediators of their children's intellectual development. This approach will primarily rely on the interaction between parents and children. From a review of previous studies, the concept of "Sustained Shared Thinking" (SST) has been identified as suitable for this research.

Sustained Shared Thinking (SST) is a process where two or more individuals engage in brainstorming and exchanging ideas to produce intellectual outcomes, such as problem-solving, processing, and describing. Previous studies have shown that SST is effective for cognitive development in preschool children. Incorporating SST into play makes the activity enjoyable, encouraging children to share their thoughts for a longer period. Therefore, the research team will include SST in play activities that parents can do with their children, using a workbook as a medium because it is convenient and easy to follow for parents. The activities in the workbook will align with the developmental stages of preschool children.

Regarding the assessment of parental empowerment, the research team developed an evaluation tool based on Zimmerman's theory, which divides empowerment into three components: psychological, interactional, and behavioral. These components are further divided into 12 subcategories, all of which are covered in the questionnaire developed by the research team.

Currently, no research has studied the effectiveness of SST activities in empowering working parents. Thus, the primary objective of this research is to study the effectiveness of SST in empowering parents. Additionally, the secondary objective is to explore the mechanisms that mediate the relationship between SST and parental empowerment, specifically focusing on parents' perception of their child's developmental progress, stimulated by parental involvement. The results of this study could guide sustainable child development in the future.

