### 6.2 Secondary Objectives

- To study the effectiveness of activities that focus on idea-sharing in enhancing parents' awareness of their child's developmental progress, stimulated by parental involvement.
- To examine the factors affecting the effectiveness of Sustained Shared Thinking activities in empowering parents and enhancing their perception of their child's developmental progress.

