## 8. Research Design and Methodology

### 8.1 Research Design

- This is a quasi-experimental study.

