## 8.4 Population Size

- **Sample Size:**

This quasi-experimental study aims to compare the means before and after the experiment. Since no prior study is available, there's no reference data for calculating the sample size. The sample size is estimated using G power software version 3.1.9.7, specifying a statistical test as paired t-tests and a power analysis as A priori: Compute required sample size. A significance level  $\alpha=0.05$ , a test power of 0.9 (90%), and an effect size  $d=0.5$  (medium) were used for calculations. The estimated sample size was at least 44 participants. To compensate for potential loss of participants due to follow-up issues or incomplete data (20% attrition), the final sample size is set at 55 participants.

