## 8.5 Variables

**Independent Variables:**

- **Parental Factors:** Age, gender, education, occupation, income, marital status, household size, number of children, time spent with children.
- **Child Factors:** Age, gender, temperament.
- **Activity:** Sustained shared thinking-based activity.

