## 8.6 Variable Definitions

- **Sustained Shared Thinking-Based Activity:** Activities conducted between parents and children that involve brainstorming and idea exchange to generate cognitive outcomes, with tools created by the research team as mediators.

- **Parental Empowerment:** The psychological process and outcomes where parents feel capable of managing and handling parenting roles effectively.
- **Perception of Children's Development:** Parents' recognition of their child's progress in thinking, reasoning, and language skills.

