### 8.8 Research Methodology

1. Obtain research approval from the Ethics Review Committee of the Faculty of Medicine Vajira Hospital, Navamindradhiraj University.
2. Develop questionnaires on parental empowerment and perception of children's cognitive development.
3. Conduct a review by experts.
4. Assess reliability and validity.
5. Develop sustained shared thinking activities for the research.
6. Advertise the study through community leaders and contact schools with kindergarten levels to reach more parents.
7. Select participants according to the inclusion and exclusion criteria.
8. Provide research information and request consent via Line (consent will be obtained by filling out the name and pressing the consent button in a Google form). Participants' identities will also be verified by sending a photo with their child to the research team.
9. Collect baseline data, including general information and questionnaires on parental empowerment (15 minutes to complete via Google form on Line or phone interview if necessary).
10. Explain the activity details that parents need to conduct with their children for 6 weeks. Tools and manuals created by the research team will be provided. Activities will be sent weekly, requiring at least one 25-30 minute session per week. Parents must send photos of completed tasks and reflection questions weekly.
11. Collect data after the 3rd and 6th (final) activity sessions, and three months after the final session using questionnaires on parental empowerment and children's cognitive development, as well as open-ended questions about their experience (15-20 minutes to complete).
12. Verify completeness of questionnaires and analyze the data statistically.

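### With every parent given the activity and no comparison group, the mediation aim and the factors-affecting-effectiveness aim can yield only associations with change over time, and sections 5 and 6.2 should be reconciled on that basis

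*Protocol*

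**What the plan says.** **Aims.** The last paragraph of protocol section 5 states that "the secondary objective is to explore the mechanisms that mediate the relationship between SST and parental empowerment" and names the parent's perception of the child's developmental progress as the mechanism. Section 6.2 does not mention mediation. It makes perception an outcome in its own right and adds a second aim: "To examine the factors affecting the effectiveness of Sustained Shared Thinking activities in empowering parents" and in enhancing perception.

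**Design.** Section 8.1 says "This is a quasi-experimental study" and section 8.4 says "This quasi-experimental study aims to compare the means before and after the experiment". Section 8.8, step 10, applies to all participants: "Explain the activity details that parents need to conduct with their children for 6 weeks", "requiring at least one 25-30 minute session per week". No comparison group appears anywhere. Section 8.5 nevertheless lists "Sustained shared thinking-based activity" among the independent variables, beside nine parental and three child factors.

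**Measurement.** Section 8.6 defines perception as "Parents' recognition of their child's progress in thinking, reasoning, and language skills". The same parent completes the empowerment questionnaire. Step 9 of section 8.8 names general information and the empowerment questionnaire at baseline, but not the perception questionnaire.

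**Analysis.** Section 8.11 compares both scores over four occasions, the first before the activities, by ANOVA and a linear mixed model.

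**The concern.** To mediate, and to affect effectiveness, are causal notions. Both need a contrast between having and not having the activity. Here that contrast is the same as before versus after. Any change also contains the child's maturation, repeated completion of the same questionnaires, and regression to the mean, because section 8.3 selects parents who report low parenting energy.

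For the mediation aim there is a second difficulty: one parent reports both perception and empowerment on the same occasions, so passing mood or response style can link the two scores.

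At stake is what the trial may conclude. A positive result could be presented as a mechanism or as an effect modifier when the data would look the same without either. A later SAP cannot cure this, because no model supplies a missing comparator.

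**Working it through.** **1. The plan's own figure.** Inputs from section 8.4: paired t-test, d = 0.5, alpha 0.05, power 0.90, 20% attrition. With n = 44, the noncentrality is 0.5 × √44 = 3.317 on 43 df, and two-sided power is 0.9000. Then 44 / (1 − 0.20) = 55. Both stated numbers reproduce. They size a before-after change in a mean, not mediation or effect modification.

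**2. Identification.** With activity = 1 for everyone, the design matrix [intercept, activity] has rank 1, so there is no between-group estimate of any path from the activity. In before-after form:

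- mean change = activity effect + natural change;
- slope of change on a factor = slope of the activity effect on it + slope of natural change on it.

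Each line has one observable and two unknowns. The left-hand sides can be estimated; the activity's share cannot.

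**3. What a before-after mediation test would show under no activity effect.** Simulation with n = 44 and 3,000 trials per cell. Changes in perception and empowerment have SD 1, a common mean drift and a correlation r. Mediation is declared when both the mean change in perception and the slope of empowerment change on perception change have p < 0.05. The protocol gives no drift or correlation, so the ranges are assumptions.

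| r between changes | drift 0 | drift 0.3 SD | drift 0.5 SD |
|---|---|---|---|
| 0 | 0.2% | 2.4% | 4.4% |
| 0.3 | 2.7% | 24.8% | 46.9% |
| 0.5 | 4.4% | 44.9% | 84.7% |
| 0.7 | 4.8% | 49.2% | 90.3% |

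The problem needs both ingredients: natural drift, and a correlation such as same-rater reporting produces.

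**4. Factors.** Take a factor that only predicts natural change and modifies no activity effect. With n = 44 and 4,000 trials, it is significant at 0.05 in 27%, 52%, 78% and 94% of trials when its correlation with change is 0.2, 0.3, 0.4 and 0.5. These would be genuine predictors of change, wrongly read as modifiers of effectiveness.

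**5. Multiplicity, as illustration only.** If the 9 + 3 = 12 factors in section 8.5 were tested one at a time at 0.05, independently and with none related to change, the chance of at least one false positive is 1 − 0.95^12 = 0.46 for one outcome and 1 − 0.95^24 = 0.71 for two.

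**6. Why a lagged change term is no remedy.** One might relate perception change (baseline to 3rd session) to empowerment change (3rd to 6th session). Both contain the 3rd-session scores, with opposite signs. Assume stable true scores, equal error variance s² and same-occasion error correlation ρ, with no other error correlation. The covariance is then −ρs², each change has variance 2s², and the correlation under no true link is −ρ/2, for example −0.25 at ρ = 0.5.

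**7. Baseline.** Section 8.11 analyses perception before the activities, and the pre-test table in section 8.12 has a row for cognitive development. Step 9 of section 8.8 does not list the questionnaire that would supply these scores.

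**The case against.** The protocol uses the modest verbs explore and examine, and the mediation aim stands in a background paragraph, not among the formal objectives. Within-parent associations and factor-by-time terms can be computed from the planned data. Much of this is sound, and several stronger readings should be set aside.

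- A reader might infer that nothing can be estimated. That goes too far: associations with change can be; the attribution to the activity cannot.
- A reader might infer that the trial will publish causal claims. The text supports only that the aims are worded causally.
- A reader might see a contradiction in perception being a mediator in section 5 and an outcome in section 6.2. A mediator is itself affected by the exposure, so the roles are compatible, and the framework figure is not available to check. What does need reconciling is that section 6.2 has no mediation aim.
- A reader might extend the same-rater argument to all factors. It does not fit age, gender, education or income; there the fault is the missing comparator.
- The activity is not strictly constant, since one weekly session is a minimum. But extra sessions are chosen by the parent, so that variation does not identify an effect.
- A reader might take 71% as this trial's false-positive rate. The protocol does not say that twelve factors will be tested singly on two outcomes, and factor selection may be left to a SAP.

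The wording of step 9 may also not be exhaustive, so the missing baseline questionnaire is probably an omission from the list and not a decision.

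**Conclusion.** The point stands for both secondary aims. As designed, neither mediation through perception nor modification of effectiveness by parent or child factors is identified as an effect of the activity. This follows from the single treated group and needs no numerical assumption.

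The size of the risk does depend on assumptions. With shared drift of 0.3 to 0.5 SD and a correlation between changes of 0.3 to 0.7, false declarations of mediation run from about 25% to 90%. With either ingredient absent they stay at or below about 5%.

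The planned primary comparison and its sample size are not altered by this point. What changes is the claim the secondary results can carry, and the objectives should be corrected before those results are interpreted.

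**What to change.** 1. Delete the mediation wording in section 5, or restate it identically in sections 5 and 6.2 as an exploratory association between changes in perception and changes in empowerment, with no claim of mechanism.
2. Reword the factors aim in section 6.2 as predictors of change in empowerment and perception over time. Estimate these as baseline-factor-by-time terms in the mixed model already planned, report them with confidence intervals, and label them exploratory.
3. Add the perception questionnaire to the baseline collection in section 8.8, step 9, so that it agrees with section 8.11.
4. Do not use a lagged change-on-change term that shares the 3rd-session scores.

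The cost is a few sentences, some factor-by-time terms in an existing model, and one more questionnaire at baseline if it is not already intended. The real price is a weaker claim about mechanism and effect modifiers. Keeping the causal wording would require a concurrent comparison group.

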## 6. Objectives

### 6.1 Primary Objective

- To study the effectiveness of activities focused on Sustained Shared Thinking in empowering parents.

### 6.2 Secondary Objectives

- To study the effectiveness of activities that focus on idea-sharing in enhancing parents' awareness of their child's developmental progress, stimulated by parental involvement.
- To examine the factors affecting the effectiveness of Sustained Shared Thinking activities in empowering parents and enhancing their perception of their child's developmental progress.

## 7. Research framework

[figure not shown]

## 8. Research Design and Methodology

### 8.1 Research Design

- This is a quasi-experimental study.

### 8.2 Target Population

- Parents (fathers or mothers) and their children aged 4-6 years.

### 8.3 Inclusion, Exclusion, and Termination Criteria

#### Inclusion Criteria:

- Parents aged over 18 years.

- Parents with children aged 4-6 years.
- Parents who live with their children.
- Parents who feel a lack of energy in parenting (based on a questionnaire conducted during the recruitment phase)

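### One uncontrolled before/after group, selected on a low self-reported state, cannot support the effectiveness conclusion in Protocol 6.1 and section 10, and section 12 does not list this as a limitation

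*Protocol*

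**What the plan says.** - **Entry (Protocol 8.3).** Inclusion is limited to "Parents who feel a lack of energy in parenting (based on a questionnaire conducted during the recruitment phase"). Neither the cut-off nor the instrument is given.
- **Design (8.1, 8.4).** "This is a quasi-experimental study", and "This quasi-experimental study aims to compare the means before and after the experiment". The size comes from G*Power, "specifying a statistical test as paired t-tests", with d = 0.5, alpha 0.05 and power 0.9. "The estimated sample size was at least 44 participants", raised to 55 for 20% attrition.
- **Conduct (8.8).** Selection is step 7, consent step 8, baseline empowerment step 9. Step 10 gives the activity to every parent. Step 11 repeats the questionnaire after the 3rd and 6th sessions and three months after the last one.
- **Analysis (8.11, 8.12).** Scores are compared across the four time points by ANOVA and a linear mixed model. The comparison table has pre-test, post-test, t and p-value columns and no group column.
- **Conclusion sought (6.1, section 10).** "To study the effectiveness of activities focused on Sustained Shared Thinking in empowering parents". Section 10 lists effectiveness as an expected benefit.
- **Limitations (section 12).** Only participants' familiarity with the remote technology is named.

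**The concern.** Three features combine: entry depends on a low self-reported state, the only comparison is each parent's own earlier score, and the conclusion is causal. The outcome is a self-report completed up to four times by parents who know they are in the programme. Scores may rise because parents recover from a low point, because they have seen the form before, because they expect to improve, or because time has passed. Nothing in the design separates these from an effect of the activities.

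At stake is the primary conclusion. The 5% error rate of a paired test protects against chance when the expected change is zero. It does not protect against a non-zero change with another cause. A study run exactly as planned could therefore report effectiveness on the strength of drift. An analysis plan cannot repair this, because the comparator is missing from the design.

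**Working it through.** **1. The plan's own figure.** Inputs from 8.4: paired t-test, d = 0.5, alpha 0.05, power 0.90. Sidedness is not stated. With the noncentral t, two-sided, power is 0.893 at n = 43 and 0.900 at n = 44, so n = 44 is reproduced (one-sided would give 36). Attrition: 44 / 0.8 = 55. The sample-size arithmetic is correct.

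**2. Smallest change that is significant.** t(0.975, 43) / √44 = 2.017 / 6.633 = 0.30 SD of change. At n = 55 it is 0.27.

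**3. Non-specific drift with zero true effect.** The rejection rate is the power of the same test at noncentrality δ√n, where δ is the assumed upward drift in SD of change:

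| δ | n = 44 | n = 55 |
|---|---|---|
| 0 | 5% | 5% |
| 0.1 | 10% | 11% |
| 0.2 | 25% | 31% |
| 0.3 | 49% | 59% |

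**4. Regression to the mean with a separate baseline, as 8.8 describes.** Let S be the screening score, B baseline and F follow-up, all standardised normal, with the lowest fraction q selected on S. Let c = Φ⁻¹(q), λ = φ(c)/q and k = λ(λ + c). Then

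- mean change = (r_SB − r_SF) λ
- variance of change = 2(1 − r_BF) − (r_SB − r_SF)² k
- δ = mean change / √variance

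For q = 0.5, λ = 0.798 and k = 0.637. For q = 0.25, λ = 1.271 and k = 0.758. All correlations and fractions are assumed. Rejection rates at n = 44:

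| r_SB, r_SF, r_BF | lowest half: δ, rate | lowest quarter: δ, rate |
|---|---|---|
| 0.7, 0.7, 0.7 | 0, 5% | 0, 5% |
| 0.7, 0.6, 0.6 | 0.090, 9% | 0.143, 15% |
| 0.8, 0.7, 0.7 | 0.104, 10% | 0.165, 19% |
| 0.5, 0.35, 0.7 | 0.156, 17% | 0.250, 37% |
| 0.8, 0.6, 0.6 | 0.181, 22% | 0.290, 47% |
| 0.8, 0.6, 0.7 | 0.211, 28% | 0.337, 59% |

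Worked line (0.8, 0.6, 0.7, lowest half): mean = 0.2 × 0.798 = 0.160; variance = 0.6 − 0.04 × 0.637 = 0.575; δ = 0.160 / 0.758 = 0.211. A steeper fall, 0.9 to 0.6 with r_BF = 0.6, would give 44% and 82%.

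**5. The case the protocol does not describe: the screening score used as the baseline.** Set r_SB = 1 and r_SF = r_BF = r. For r from 0.8 down to 0.6 the rate at n = 44 is 39% to 70% (lowest half) and 64% to 93% (lowest third).

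**6. Precision of a drift-corrected contrast.** With two pre-activity forms B1 and B2 and a later score Y, the contrast is (Y − B2) − (B2 − B1) = Y − 2B2 + B1. Under compound symmetry its variance is 6σ²(1 − r), against 2σ²(1 − r) for Y − B2. The SE ratio is √3 ≈ 1.73. The planned d = 0.5 becomes 0.5 / 1.73 = 0.289, with power about 47% at n = 44 and 56% at n = 55.

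**The case against.** The strongest reply is that the protocol keeps screening and baseline apart. Section 8.7 has parents enter initial information by QR code and be contacted afterwards if eligible, and 8.8 collects baseline empowerment after selection and consent. The screen concerns energy in parenting; the outcome is a questionnaire with three components and 12 subcategories (section 5). Nothing says they are one instrument. This stands. A reader might infer from 8.3 that the low entry score is itself the starting point of the comparison, and so that false significance runs at 39% to 93%. The documents do not support that reading. Nor is there a need to tell the sponsor to keep the recruitment questionnaire out of the baseline, since 8.8 already does so.

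The separation does not settle the matter. No interval between screening and baseline is stated. If they are close together, the screening score may well correlate more with baseline than with follow-up, and some regression remains.

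Second, drift has no known size or direction. Section 9 says the activities take effort and could affect parents' mental health, so change could be downward, and pre-test collection spread over months 5 to 7 partly blurs calendar effects. This also stands: the percentages show what drift of a given size would do, not what will happen.

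Third, the design is openly called quasi-experimental, and no rule equates p < 0.05 with effectiveness. A reader might infer such a rule; it is not written. But naming the design does not license the conclusion worded in 6.1 and section 10, and section 12 is silent on it. Expert review and validation of the questionnaire (8.8) and keeping the exercise designers out of selection and analysis (8.10, 8.11) are useful, but they do not address drift.

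**Conclusion.** The concern holds as a mismatch between design and conclusion. One group of parents selected on a low self-report and compared only with itself can show change in empowerment during the programme. It cannot show that the activities caused the change. The sample-size calculation is not at fault.

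For size, the firmest figure is that an upward drift of 0.2 to 0.3 SD of change, with no true effect, is significant in 25% to 49% of trials at n = 44. Regression to the mean ranges from no contribution, under equal correlations, to the decay-case rates in the table above, up to 59% for a fall of no more than 0.2. The protocol gives no drift size, correlation, cut-off or selected fraction, so these are conditional illustrations and not estimates of this trial's error rate. The absence of a second group is itself inferred: the protocol never says single arm, but 8.4, 8.8, 8.11 and 8.12 describe only one group.

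**What to change.** **1. Wording (needed).** Reword 6.1 and section 10 so that the conclusion is change in parental empowerment during the programme. Add to section 12 the absence of a control group, possible regression to the mean after selection on a low state, and repeated-questionnaire effects. Cost: text only.

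**2. A second pre-activity form (a cheap improvement).** Send the empowerment form at consent and again about 3 weeks later, just before activity 1. Use the second as baseline in all contrasts. Report the no-activity change between the two, with its 95% CI, beside the change from baseline to the 3rd session.

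The cost is one extra 15-minute online form and about 3 weeks per parent. The timetable in section 14 is already tight: activities run to month 9, so a three-month follow-up of the last parents falls near month 12 (9 + 3), while post-test collection is shown ending in month 10. The drift-corrected contrast has an SE about 1.7 times larger, covers only the 3rd session, and cannot remove expectancy effects that begin with the activities. It should be supportive and should not replace the primary contrast.

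Keeping the effectiveness wording would call for a concurrent or waiting-list control. For scale, a standardised between-group difference of 0.5 at two-sided 0.05 and 90% power needs 86 evaluable per arm, or 86 / 0.8 = 107.5, so 108 enrolled per arm. This is a much larger study and is not required if the wording is changed.
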